### *Secondary outcome measures*

For binary outcome measures (e.g. LCOS), logistic regression analyses will be used including age group and physiology as fixed effects, and site as a random effect, with unadjusted and adjusted odds ratios (ORs) and 95% CIs reported (Table 3). Survival outcomes (length of PICU stay, length of hospital stay) will be visually presented using a Kaplan-Meier plot and a Cox proportional hazard model will be used to assess differences between treatment groups with

treatment group and stratification variables as fixed effects and site as a random effect (i.e. utilising a shared frailty model). The hazard ratio and 95% CI will be presented as an estimate of treatment effect. Continuous outcomes (e.g. PELOD-2, duration of renal replacement therapy) will be analysed using linear regression adjusting for age group and physiology as fixed effects, and site as a random effect, with mean difference and 95% CI reported. If the residuals demonstrate non-normality, quantile regression will instead be used in the same manner as for the primary outcome. Key assumptions of the models will be tested and reported on (for logistic regression: specification, goodness-of-fit, absence of multicollinearity and absence of influential observations; for survival analysis: proportionality assumption, goodness-of-fit; for linear regression: specification, distribution of residuals, homoscedasticity, absence of multicollinearity, linearity).

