### 7.3 Blood Sample Collection for Inflammation analysis

**Biomarker Analysis and Biobanking:** Blood markers for myocardial injury and inflammatory response will be collected on induction of anaesthetics (baseline – pre bypass), at admission to PICU (0 hours – post bypass) and at 12, and 24 hours for the following purposes: i) to test the impact of the intervention on markers of inflammation; ii) to stratify patients in to high- versus low inflammatory groups; iii) to biochemically define responders to the intervention (to identify patient subgroups that are more likely to respond to a specific treatment), iv) to develop improved markers of outcome post cardiac surgery. Collection of blood for biomarker analysis and biobanking is optional and parents will be asked to provide their permission during the consenting process.

**Blood sampling and processing.** *Preoperative baseline* (before onset of cardiac surgery, done by anaesthetist during the induction of the patient once the arterial line has been inserted): 1-2ml of EDTA blood (for DNA), 2.5ml of blood (PAXgene tube for gene expression markers), 1-2ml of serum *Postoperative at 0,12,24 hrs* (in PICU until discharge to the ward): 2.5ml of blood (PAXgene tube - time point 0 only), 1-2ml of serum. The total amount of blood taken is 10-15ml for the entire study duration, which is much less than the amount of blood taken for routine perioperative care tests. The samples will be processed within 30 minutes, centrifuged, aliquotted and immediately frozen. The samples will be kept in a security protected freezer in the each institution, and will be transferred in batch every 12 months to the Centre for Children's Health Research, Brisbane, Australia. Urinary electrolytes and NH4 will be measured from patient urine collected through the

standard IDC at baseline, admission to PICU, and 6-24hours to assess for renal concentration and secretory function. Paired arterial and venous gases will be collected postoperatively at 0,6,12,24,48 hrs (in PICU until discharge to the ward or removal of arterial line, whichever occurs first) to assess for lactate and SaO2-SvO2 gradient. Each arterial or venous blood gas sample requires 0.2mls of blood and would total 2mls across all samples. Routine paired gases are often part of standard clinical care.

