## 11 STATISTICAL METHOD

### 11.1 ANALYSIS PLAN

**Data Analysis.** Descriptive statistics will be utilised to report on the baseline characteristics of the total study cohort and each subgroup, as well as by site. The primary outcome measure investigating length of mechanical ventilation will be analysed using a Mann-Whitney test (assuming the data is non-normally distributed). Analysis of secondary outcomes includes both comparisons of measurements and proportions, using confidence intervals of differences as the major method of presentation where possible, otherwise standard techniques such as Mann-Whitney U tests, t-tests and chi-squared tests will be utilised. All analyses will be by intention-to-treat. Statistical significance will be set at the 0.05 level for the primary outcomes. Post-hoc power analyses may be undertaken to determine if results found in sub-group analyses are reliable.

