## **Sample size**

Pilot study data demonstrated a 66 hour (0.33 SD) reduction in VFDs associated with the study intervention [26]. Assuming a minimally clinically significant small effect size (0.2 SD), 90% power, two-sided alpha level of significance of 5%, 10% withdrawals, and 15% increase in sample size to account for a non-normal distribution of VFD, 1,320 patients are required (660 per group).

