## **Statistical analysis**

### *Statistical analysis principles*

- Analyses will be conducted based on the intention-to-treat principle. Specifically, patients who are eligible, who do not meet any exclusion criteria and who undergo randomisation will be analysed based on the treatment group they were allocated to, independent of the compliance with the treatment delivered.
- Participants who had more than one surgery before their second birthday will only have data related to their first surgery for which study consent was available analysed.
- Statistical tests will be two-sided applying a statistical significance level of 0.05. As we are not correcting for multiplicity when comparing secondary or other outcomes, such results will be considered exploratory and will be reported as point estimates with 95% confidence intervals (CIs).
- If there is missing data for the primary outcome measure for any participants, imputation methods will be used.
- Continuous variables will be assessed for normality; this will be undertaken using visual inspection of histograms and Q-Q plots.
- Standard descriptive statistics will be used when summarising variables; frequencies (percentages) for discrete variables, mean and standard deviation (SD) for continuous

variables, or, if continuous variables are non-normally distributed, median with interquartile range (IQR).

- This analysis plan and the primary manuscript will only include analyses up to 28 days. We will present analyses of postoperative delirium, health care costs, inflammatory markers and long-term outcomes (12 months and later post procedure) separately.
- Pre-planned subgroup analyses will be performed including the pre-defined study strata; these will be executed regardless of any potential treatment effect on the primary or secondary outcomes in the main cohort.
- To ensure transparency and reproducibility, the Stata code that will be used to analyse the final study data is available on GitHub (16).
- The trial statistician will be blinded to the treatment group until the analyses outlined in this SAP have been completed.
- Changes in the analysis plan by the investigators effective after publication of this SAP will be declared as such.

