| PICU admission median (IQR)                                    |                     |                       |                       |                                       |                     |

|                                                  |  |  |  |  |  |
|--------------------------------------------------|--|--|--|--|--|
| 24 hours post-PICU admission median (IQR) |  |  |  |  |  |
| Creatinine                                       |  |  |  |  |  |
| PICU admission mean (SD)                  |  |  |  |  |  |
| 24 hours post-PICU admission mean (SD)    |  |  |  |  |  |
| Acute kidney injury: PICU admission n (%) |  |  |  |  |  |
| Stage 1 n (%)                             |  |  |  |  |  |
| Stage 2 n (%)                             |  |  |  |  |  |
| Stage 3 n (%)                             |  |  |  |  |  |
| Acute kidney injury: 24 hours n (%)       |  |  |  |  |  |
| Stage 1 n (%)                             |  |  |  |  |  |
| Stage 2 n (%)                             |  |  |  |  |  |
| Stage 3 n (%)                             |  |  |  |  |  |
| Acute kidney injury: 48 hours n (%)       |  |  |  |  |  |
| Stage 1 n (%)                             |  |  |  |  |  |
| Stage 2 n (%)                             |  |  |  |  |  |
| Stage 3 n (%)                             |  |  |  |  |  |

395 SD standard deviation; IQR interquartile range; ECLS extracorporeal life support; PICU paediatric intensive care unit; CI confidence interval  
396

397 **Supplementary Appendix**

398

399 **S1. List of approved protocol modifications**

400

| Version Number | Approval Date | List of Modifications                                                                                                                                                                                                                                                                                                                                                                                                                                                                                                                                          |

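### Troponin is compared between arms at PICU admission and 24 h separately, without the planned pre-bypass value as a covariate and without the planned 12 h sample

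*Combined protocol and SAP*

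**What the plan says.** **Sampling.** Protocol 7.3 states: "Blood markers for myocardial injury and inflammatory response will be collected on induction of anaesthetics (baseline – pre bypass"; further samples follow at PICU admission (0 h), 12 h and 24 h. The postoperative draws are made "in PICU until discharge to the ward". Parents may decline this sampling, and the part of 7.3 on biobanked blood lists Troponin I only where it is available. Protocol 6.1 starts nitric oxide once the child is on bypass, so the induction sample precedes treatment.

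**Analysis of troponin.** The SAP (Secondary outcome measures) says that continuous outcomes "will be analysed using linear regression adjusting for age group and physiology as fixed effects, and site as a random effect". If residuals are non-normal, quantile regression replaces this, as for the primary outcome. The sensitivity analysis adds bypass duration, surgical complexity, blood prime and sex. None of the three includes the outcome's own baseline. SAP Table 3 has two troponin rows, one at PICU admission and one labelled "24 hours post-PICU admission", both summarised as median and interquartile range. It has no pre-bypass row and no 12 h row. The SAP describes no repeated-measures model, and its imputation covers only the primary outcome.

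**Inflammatory markers.** The SAP (Statistical analysis principles) defers these to a separate report and gives no model for them. Protocol 11.1 puts confidence intervals for differences first for secondary outcomes, "otherwise standard techniques such as Mann-Whitney U tests, t-tests and chi-squared tests will be utilised".

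**Status.** Troponin is a physiological descriptor, reported to describe physiology only. "Statistical tests will be two-sided applying a statistical significance level of 0.05", but secondary results are treated as exploratory, without multiplicity correction.

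**The concern.** A pre-treatment measurement of the outcome is often its most useful covariate. Here the protocol plans to draw it, but the comparison of the arms does not use it. The 12 h value would add information on the same children, and on those who have left PICU by 24 h, but it too is left out.

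At stake is the precision of the trial's evidence on mechanism. Protocol 2.1 says that the pilot could not explain plausibility because it measured no direct inflammatory markers. Protocol 3.2 makes markers of inflammation and myocardial injury a secondary outcome, and troponin is the part that appears in the main report. Optional sampling already reduces the number of children who contribute.

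A second issue concerns the 24 h row. Postoperative sampling ends when the child goes to the ward, and shorter PICU stay is one of the trial's aims. If nitric oxide sent milder cases to the ward sooner, the treated children still sampled at 24 h would be a sicker selection, and a benefit could be partly hidden.

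**Working it through.** **1. The plan's own figure.** The only sizing in the documents is for ventilator-free days: "Assuming a minimally clinically significant small effect size (0.2 SD), 90% power, two-sided alpha level of significance of 5%, 10% withdrawals", and a "15% increase in sample size to account for a non-normal distribution of VFD". Per arm before inflation: 2 × (1.960 + 1.282)² / 0.2² = 525.4. With both inflations:
- 525.4 × 1.15 × 1.10 = 664.6, so 665 per arm (1,330)
- 525.4 × 1.15 / 0.9 = 671.3, so 672 per arm (1,344)
- 525.4 × 1.25 = 656.7, so 657 per arm (1,314)

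All are within 3% of the stated 1,320. This point does not touch that figure. No sizing is given for troponin or any other marker.

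**2. Gain from the baseline covariate.** In a linear model for mean log troponin, adding the baseline multiplies the residual variance by 1 − ρ² and the interval width by √(1 − ρ²). The equivalent gain in patients is 1/(1 − ρ²) − 1. Because age group, physiology and site are already in the model, ρ is the partial correlation after those terms. The documents do not give it, so the range is an assumption.

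The last two columns give the difference detectable with 90% power, (1.960 + 1.282) × √(2/n) × √(1 − ρ²), in SD units. Here n is 594 per arm (660 less 10%), or 297 if, as an assumption, only half are sampled.

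| ρ | Variance factor | Interval width factor | Equivalent extra patients | Detectable, n = 594 | Detectable, n = 297 |
|---|---|---|---|---|---|
| 0 (no baseline) | 1.00 | 1.000 | 0% | 0.188 | 0.266 |
| 0.1 | 0.99 | 0.995 | 1% | 0.187 | 0.265 |
| 0.3 | 0.91 | 0.954 | 10% | 0.179 | 0.254 |
| 0.5 | 0.75 | 0.866 | 33% | 0.163 | 0.230 |
| 0.7 | 0.51 | 0.714 | 96% | 0.134 | 0.190 |

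**3. What discharge before 24 h could do.** The documents do not give the share of children without a 24 h sample, so this was explored by simulation: 400 runs per setting and 594 per arm. Assumptions: true effect −0.20 SD, baseline correlation 0.3, correlation among post-bypass values 0.7, and nominal loss by 24 h of 10%, 20%, 30% or 40%. Baseline, 0 h and 12 h values are complete.

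| Discharge before 24 h | 24 h estimate, available cases | Estimate using baseline, 0 h and 12 h |
|---|---|---|
| Unrelated to troponin | −0.20 | −0.20 |
| Likelier with low 12 h troponin | −0.18 to −0.19 | −0.20 |
| As above, and treatment also speeds discharge (log-odds 0.3) | −0.14 to −0.16 | −0.20 |

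The largest shrinkage, about 0.06 SD, is smaller than the run-to-run SD of that available-case estimate in the same setting (about 0.08). The simulation favours the fuller model, because discharge depends only on values that the model sees and no 12 h value is missing.

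**4. Is heavy loss by 24 h likely?** Pilot mean PICU stays (Protocol 2.1, Table 1) run from 107.5 to 199.2 h across arms and age groups. The small earlier US study had 53.8 versus 79.4 h. Such stays are usually skewed, so the means do not exclude some discharges before 24 h, but they do not suggest that most children have left.

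**The case against.** The strongest reply is that this is a matter of efficiency in a descriptive outcome. Randomisation makes a comparison at a fixed time valid without a baseline term, the admission row is not exposed to discharge, and no confirmatory claim depends on troponin. That is correct and limits the weight of the point. It does not explain why a planned pre-treatment value should be left out.

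Four stronger readings are tempting, and the documents do not support them.

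- *The inflammatory markers are committed to unadjusted two-sample tests.* The SAP defers them and gives no model. The protocol's list of tests is open-ended and comes after confidence intervals. What can be said is that no baseline term has been specified.
- *The pre-bypass sample goes unused.* Protocol 3.3 and 7.3 plan to use pre-intervention markers to grade severity, form inflammatory groups and define responders. The gap is only in the main comparison of the arms.
- *The 24 h comparison is biased.* The documents show a route to bias, not its presence. The larger shrinkage above also needs an assumed effect of treatment on discharge.
- *The fix is free because every value will exist.* Sampling is optional, troponin is measured where available, and the baseline variables in Protocol 7.2 do not list it. For creatinine, SAP section S2 says that no baseline values were available. Pre-bypass and 12 h troponin may be incomplete.

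Two technical objections also stand. The strata already absorb part of the variation between sick neonates and older infants, so ρ must be read as partial. And 1 − ρ² applies to a model for the mean, not to the interval from a median regression, which is the SAP's fallback.

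On the other side, the SAP's outcome list speaks of troponin over the first 24 postoperative hours, which could cover 12 h. Table 3 does not carry that through.

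**Conclusion.** The point holds for troponin. The planned comparison omits a pre-treatment baseline that the protocol intends to draw and leaves out the 12 h value. For any non-zero partial correlation, baseline adjustment improves precision: intervals about 0.5% narrower at 0.1, 5% at 0.3, 13% at 0.5 and 29% at 0.7. These figures rest on an assumed ρ, on a model for mean log troponin, and on the baseline having been measured; they shrink in proportion to how often it is missing.

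Bias at 24 h from PICU discharge is a possible exposure. It cannot be sized from the documents and may be small.

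For the inflammatory markers the point is a request to specify the baseline term in the separate report, not a criticism of a chosen method. The primary analysis, the sample size and the exploratory status of the secondary outcomes are unaffected.

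**What to change.** Before unblinding, specify the following in the SAP.

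1. Analyse log troponin with the log pre-bypass value as a covariate, together with age group, physiology and site. Report ratios of geometric means with 95% intervals. The medians in Table 3 can stay as description.
2. Preferably, fit one repeated-measures model to the 0, 12 and 24 h values, with arm by time, including every child with at least one post-bypass value. This relies on missing values being explained by the observed ones, so say so.
3. Keep children without a pre-bypass value, either by modelling the baseline jointly with the later values or by a named missing-baseline method.
4. State whether troponin is assayed at induction and at 12 h. Report by arm how many children have a value at each time and how many had left PICU by then.
5. Carry the same baseline term into the plan for the separate inflammatory-marker report.

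The cost is SAP wording, code and slightly more analysis work. The blood draws are already in the protocol, but some assays may have to be added if troponin was not going to be measured at every draw. If pre-bypass or 12 h troponin turns out to be largely missing, the gain falls accordingly.

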#### *Safety outcomes*

Adverse drug reactions considered to be possibly, probably, or definitively related to the study treatment based on the judgement of the treating local physician, will be reported in supplementary material. Additionally, the proportion of patients with at least one adverse event will be compared between the two treatment groups using logistic regression as described above for secondary outcomes.

#### *Subgroup and sensitivity analyses*

We will undertake two subgroup analyses that were pre-defined in the study protocol:

- age: <six weeks versus  $\geq$ six weeks; and
- physiology: univentricular versus biventricular.

Subgroup analyses will be undertaken using the same analysis methods described for the primary and secondary outcome measures, with the addition of the subgroup variable and its

related interaction term into the main regression model. For each subgroup, the relevant descriptive statistics will be presented for the primary and secondary outcomes, along with the appropriate measure of effect size (and 95% CI) and interaction effect (and 95% CI and p-value). A Forest plot will be developed to present heterogeneity between the treatment group and subgroup variable, including the p-value, and presented as a supplementary figure.

Additionally, a sensitivity analysis for study outcomes will be undertaken including the following variables: treatment group, duration of CPB, surgical complexity (recorded using the risk adjustment for congenital heart surgery [RACHS] score), blood prime using during surgery, sex and strata variables as fixed effects, and site as a random effect. Results will be presented in the same manner as primary analyses and included in the supplementary material.

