## **6 INTERVENTION**

## 6.1 Treatment arms

Patients allocated to the study gas arm will receive NO, which will be blended into the fresh gas flow kept at 3L/min for the CPB oxygenator with NO levels maintained at 20 ppm via an Ikaria INOmax DSIR (Ikaria, NJ, USA) or similar device. Continuous sampling of NO and NO2 concentration will be undertaken from an access port just prior to the oxygenator. NO will be started immediately when the patient is on CPB and ceased once coming off CPB at the completion of MUFing. Patients allocated to the Placebo arm will receive standard respiratory gases (oxygen-air mix) during bypass at a flow rate of 3L/min. Partial pressures of CO2 will be maintained constantly in both study arms as per the institutional practice.

*Note:* If patients require several CPB runs during the same procedure, the treatment has to be provided for each run using the same treatment allocation for every run (i.e. patients allocated to study gas arm will receive NO at 20ppm for every run).

**Subsequent CPB procedures:** Patients that were previously enrolled and randomised into the study with surgical procedure performed that required use of cardio-pulmonary bypass will not get re-randomised. Previously enrolled and randomised patients will undergo the same treatment allocation for subsequent surgeries, unless parents opt out. The study perfusionists at each study site have access to the treatment allocation, which will remain blinded for all other study team members.

**Blinding arrangements.** Of the investigating team, only the study perfusionist will be aware of the randomisation and NO delivery. Blinding arrangements in the operating theatre will be achieved by covering the NO delivery system with drapes. The dedicated study NO delivery system will be connected to the CPB oxygenator at all times, independent of randomisation. The surgeons, anaesthetists and ICU staff will be not aware which treatment arm a patient been allocated to. The perfusionists will be advised that all aspects of CPB except for provision of NO (or not) should be performed in a standard fashion for study participants. The perfusionist does not attend the surgical handover in PICU. The Data Safety Monitoring Board will be unblinded in the event of a severe adverse event. In our pilot study and the previous published study by Checcia, methaemoglobin values using NO at 20 ppm were similar in both the control and intervention groups (1.4%) [29].

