**Study design and participants**

The NITRIC trial is a 1320-patient international, multicentre, randomised, double-blind trial in infants and children less than two years of age undergoing open heart surgery on CPB. A total of 1320 patients will be recruited across the six paediatric cardiac centres in Australia, New Zealand, and The Netherlands. Eligible patients will be randomly assigned to NO at 20 ppm administered into the CPB oxygenator for the entire duration of CPB versus standard care (no NO into the CPB) in a 1:1 ratio with stratification by age (less than six weeks; greater than or equal to six weeks), single ventricle physiology (present or not present) and study site.

The primary hypothesis is to demonstrate that NO during CPB increases VFDs compared with standard care in eligible infants. The full study protocol has been previously published (13) and specified inclusion and exclusion criteria, randomisation and blinding procedures, interventions, study outcomes including primary and secondary outcomes, process of care measures and physiological descriptors, adverse events, safety data monitoring, sample size, and data collection and management.

The study protocol has been approved by the Children's Health Queensland Human Research Ethics Committee (HREC/17/QRCH/43; original submission approved 6th March 2017). Minor modifications to the original study protocol were reviewed and approved by the HREC and are provided in Supplementary Appendix (Section S1). This SAP is based on version 1.4 of the study protocol.

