## **Randomisation**

Randomisation is conducted online through the purpose-built REDCap electronic data capture tool hosted at The University of Queensland (14, 15); the randomisation module can only be accessed by the central study coordinator and the site perfusionist, and only after a patient has been screened, is deemed to have met eligibility criteria and has provided informed consent. A randomisation sequence using variable block randomisation with a 1:1 ratio was generated and loaded into REDCap prior to screening of the first patient. Randomisation is stratified on age (<six weeks, ≥six weeks), cardiac physiology (univentricular, biventricular) and study site. The precise time of randomisation occurs variably prior to starting CPB dependent on site logistics, and the intervention begins with start of CPB.

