## **Surgical procedure and intervention characteristics**

We will provide details on the surgical procedure by treatment group, including concomitant therapies (Table 2). We will compare characteristics of the procedure that in principle may be altered by the intervention (for example, duration of CPB, duration of aortic cross-clamp) between the two study arms by presenting descriptive statistics along with estimate of difference and 95% confidence interval (CI).

We will report on the compliance with the study drug (NO) using a number of measures, reported for patients randomised to the intervention group only (Table 2). Additionally, we will list protocol deviations relating to the administration of NO in supplementary material.

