## **Outcome measures analysis**

### *Primary outcome measure*

The primary outcome measure (VFDs censored at 28 days after CPB start) will be analysed using a Mann-Whitney test with differences between medians calculated by quantile regression using the simplex algorithm, inclusive of stratification variables (age group and physiology) and site included as fixed effects in the model. The effect estimate, corresponding 95% confidence interval (CI) and p-value will be presented. The unadjusted p-value using a Mann-Whitney test will also be presented (Table 3).

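### The supplementary sensitivity model adjusts for duration of bypass, which the SAP says nitric oxide may alter, so it need not estimate the intention-to-treat effect

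*Combined protocol and SAP*

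**What the plan says.** **The sensitivity model.** Under Subgroup and sensitivity analyses, the SAP says that "a sensitivity analysis for study outcomes will be undertaken including the following variables: treatment group, duration of CPB, surgical complexity", followed by blood prime, sex and the strata as fixed effects and site as a random effect. No outcome is exempted. The results go to the supplement but are laid out like the primary analyses. The text does not call this a mediation or direct-effect analysis and gives no caveat.

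**Timing.** The SAP's Randomisation section says: "The precise time of randomisation occurs variably prior to starting CPB dependent on site logistics, and the intervention begins with start of CPB". Its Study design and participants section describes the treatment as "NO at 20 ppm administered into the CPB oxygenator for the entire duration of CPB".

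**The SAP's own view of CPB duration.** Under Surgical procedure and intervention characteristics, it plans to compare between arms the "characteristics of the procedure that in principle may be altered by the intervention (for example, duration of CPB, duration of aortic cross-clamp"). SAP Table 2 has a row for CPB duration with a column for the difference and its 95% confidence interval.

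**Contrast.** The primary model is "inclusive of stratification variables (age group and physiology) and site included as fixed effects in the model". Protocol section 3.3 pre-plans adjustment for preoperative surgical risk (RACHS and Aristotle scores) and does not mention CPB duration.

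**The concern.** A sensitivity analysis with extra covariates is normally read as a robustness check: the same treatment effect, estimated with better control of prognosis. That reading requires covariates that treatment cannot affect. CPB duration does not meet the requirement on the SAP's own account, because one section treats it as a possible consequence of NO and another adjusts for it as if it were a baseline factor.

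Two problems follow if NO does change time on bypass. Adjustment removes whatever part of the effect works through a shorter or longer bypass. It also conditions on a variable that may share unmeasured causes with the outcome, such as a difficult repair, and this can create an association between treatment and outcome that randomisation had excluded.

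A further overlap adds to this. The SAP counts ventilation and length of stay from the start of CPB, so time on bypass is already inside those outcomes.

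At stake is the interpretation of one set of supplementary results. A difference from the main analysis might be read as fragility, or agreement as confirmation, when the two models need not target the same quantity.

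**Working it through.** **1. The yardstick.** The SAP sizes the trial for 0.2 SD with 90% power and two-sided 5% alpha. The normal-theory formula gives 526 per arm. With the 10% and 15% allowances, the total is:

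- 2 × 526 × 1.10 × 1.15 = 1331
- 2 × 526 × 1.15 / 0.90 = 1344
- 2 × 526 × 1.25 = 1315

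All are within 2% of the stated 1320, so 0.20 SD is a fair reference effect. Nothing below depends on the sample size calculation.

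**2. The timing argument.** Randomisation precedes CPB, NO starts with CPB, and NO continues throughout it. CPB duration is therefore fixed only when treatment ends. It also sets the length of exposure in the NO arm.

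**3. Formula.** Work in SD units, with a linear model for a mean. Let

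- a = effect of NO on CPB duration
- b = effect of CPB duration on outcome
- c = effect of an unmeasured intra-operative factor on CPB duration
- d = effect of that factor on outcome

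The treatment coefficient after adjusting for CPB duration is

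adjusted effect = total effect − a × (b + c × d).

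The error is zero if a = 0, or if b and c × d are both absent or cancel.

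**4. Inputs.** The total effect of 0.20 SD comes from the SAP. The documents give none of a, b, c or d. Assumed values are b = −0.4 (longer bypass, worse outcome), and either no unmeasured factor or c = 0.5 and d = −0.4 (the factor lengthens bypass and worsens outcome). The value of a is varied.

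**5. Results.** For a = −0.1:

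- without the factor: 0.20 − (−0.1)(−0.4) = 0.16
- with the factor: 0.20 − (−0.1)(−0.4 − 0.2) = 0.14

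| a (SD of CPB time) | True total effect | Adjusted, no unmeasured factor | Adjusted, with factor |
|---|---|---|---|
| 0 | 0.20 | 0.20 | 0.20 |
| −0.1 | 0.20 | 0.16 | 0.14 |
| −0.2 | 0.20 | 0.12 | 0.08 |
| +0.2 | 0.20 | 0.28 | 0.32 |
| −0.2 | 0 | −0.08 | −0.12 |
| +0.2 | 0 | +0.08 | +0.12 |

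Simulation with 400,000 records per setting agreed to within 0.01. For example, it gave 0.163 and 0.144 for a = −0.1 with a true effect of 0.20.

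With b = 0 and only the unmeasured factor acting, a = −0.2 still moves 0.20 to 0.20 − (−0.2)(−0.2) = 0.16. Bias therefore does not need CPB duration itself to affect outcome.

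**6. What the planned comparison of CPB duration can show.** With 660 per arm, the 95% confidence interval for a difference in SD units has half-width 1.96 × √(2/660) = 0.108. This is approximate, since CPB time is probably skewed. An interval centred on zero would leave room for an error of up to 0.108 × 0.4 = 0.043 SD, or 0.108 × 0.6 = 0.065 SD with the assumed factor. Larger errors would be ruled out under these assumptions.

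**The case against.** The strongest reply is that the consequence is small. The analysis is supplementary and decides nothing, and the SAP already calls secondary and other outcomes exploratory. The hypothesised pathway in protocol section 2.2 runs through myocardial injury, inflammation and low cardiac output syndrome, not through time on bypass. If NO does not alter CPB duration, the linear-model bias vanishes. All of this stands. It limits the weight of the point but does not remove it, because the SAP itself leaves open that CPB duration may change.

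A reader might infer more than the documents support:

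- **That this is the trial's only covariate-adjusted check.** The primary model already adjusts for age group, physiology and site, with an unadjusted Mann-Whitney p-value beside it. Binary secondary outcomes get unadjusted and adjusted odds ratios.
- **That agreement or disagreement with the main analysis could never be interpreted.** The planned comparison of CPB duration by arm is a partial diagnostic. It bounds large distortions, though not small ones (step 6).
- **That a definite share of the effect will be lost.** Every input except 0.20 SD is assumed. Only a shortened bypass pulls a beneficial estimate down under these assumptions; a lengthened one pushes it up. The identity also concerns linear means, whereas the SAP plans quantile regression for ventilator-free days and logistic and Cox models for others. The figures do not transfer to those models.
- **That blood prime must go too.** It is true that "only the study perfusionist will be aware of the randomisation and NO delivery" within the investigating team. But no section says the prime is chosen after allocation is known, protocol section 6.1 tells perfusionists to keep every other aspect of bypass standard, and protocol section 2.1 mentions priming among practice differences in its argument for a multi-centre trial. A clarification is enough.
- **That surgical complexity is equally suspect.** The protocol records RACHS with the procedure performed, but section 3.3 treats it as preoperative risk and SAP Table 1 lists it at baseline.

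**Conclusion.** The point holds as a limited one. The sensitivity model conditions on a variable that arises after randomisation, during treatment, and that the SAP says treatment may alter. If NO changes CPB duration, the adjusted estimate is not the total intention-to-treat effect and can be too small or too large. If it does not, there is no bias in a linear model.

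The size is unknown. As an illustration only, a 0.1 SD shortening would turn 0.20 SD into about 0.16 SD, or about 0.14 SD with the unmeasured factor. This rests on linearity, a slope of −0.4 SD and the assumed strength of that factor.

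Nothing here touches the primary analysis, the main secondary models or the sample size. The change is worth making because the results will look like the primary results and will be read as a check on them.

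**What to change.** In the SAP's Subgroup and sensitivity analyses section, remove duration of CPB from the covariate list. Keep RACHS, sex, the strata and site. Report CPB duration by arm, with its difference and 95% confidence interval, as the SAP already plans.

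If a model with CPB duration is wanted, present it separately, label it exploratory, and state that it does not estimate the total effect of allocation to NO.

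Blood prime can stay, with one added sentence saying whether it is fixed before the allocation is known.

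The cost is an edit to the SAP text and the matching line of analysis code. The SAP already commits to declaring changes made after its publication. The small loss is that readers who expect a CPB-adjusted model would no longer find one among the main robustness checks.
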